### C-reactive protein test

We will use a bedside, lateral flow chromatic immunoassay-based CRP test kit, Actim^©^ CRP test kit ([name]), that provides a semi-quantitative assessment of CRP. These will have been validated across all sites. A paediatric nurse will use a lancet to obtain a drop of blood from the fingertip or sole of the young infant with no signs of CSI or critical illness after 48 hours of hospitalisation using the WHO guidelines on drawing blood [30]. Consent for this sample will be taken at the time of screening. The sample will be processed as per kit instructions. A positive result can be read as soon as it becomes visible. One, two, and three blue lines correspond to a CRP of 10-40 milligrammes (mg) / litre (l), 40-80 mg / l, and >80 mg / l, respectively. A negative result, which corresponds to less than 10 mg / l of CRP, is indicated by the presence of only a red control line and should be confirmed at five minutes. Based on the results of the test, the treating physician will decide whether the young infant is eligible to be enrolled. There is no major risk associated with the test. However, bruise or mild soreness around the blood test site is common and can last for a few days.

Eligible infants will be enrolled if their parents provide informed written consent to participate in the study. They will be randomised to either continued hospitalisation for up to a total of seven days or discharged from the hospital on home treatment with an oral antibiotic for the next five days. Based on the findings of the systematic review (unpublished data), it was decided that a single, semi-quantitative (threshold level 10 mg / l) CRP will be performed 48 hours after admission for enrolment.

### Intervention

Discharge from the hospital and home treatment with oral amoxicillin for five days.

### Control

Continued injectable antibiotic treatment and supportive therapy in the hospital for seven days.

One of the possible reasons that outpatient care was observed to be better than hospital care in previous studies might be the poor quality of care in hospitals. In this study, we would like to reduce this factor as far as practically feasible. This means that the quality of care at the study hospitals will be reviewed against the WHO pocketbook for hospital care for children [4] and will be improved using quality improvement approaches to ensure a “minimum” quality of hospital care. Efforts to improve the quality of care will also be made at outpatient facilities.

### Outcomes

The primary outcome is “poor clinical outcome” defined as 1) death between randomisation (day three of initiation of therapy) and day 15 of initiation of therapy, or 2) presence of any sign of critical illness (no movement at all, unable to feed at all, or convulsions) or any sign suggestive of another serious infection, e.g. meningitis, bone or joint infection, on day four and eight of initiation of therapy, or 3) presence of any sign of CSI on day eight of initiation of therapy.

### Screening and enrolment

Young infants up to two months of age at the outpatient or emergency department will be examined, triaged, and stabilised by the consulting paediatrician or physician of the participating hospital. This process followed as part of regular facility procedures is referred to as “pre-screening”. If the paediatrician / physician observes signs of CSI during their initial assessment and the clinical condition of the infant is stable, the infant will be assessed by the study screening, enrolment and randomisation team. Screening of sick young infants will be performed by a study nurse / physician in the outpatient or emergency department of the participating hospital, and information will be captured on the case report form (screening and pre-enrolment form). Those who fulfil the above-mentioned inclusion criteria and do not have any exclusion criteria will be pre-enrolled after confirmation of clinical signs by the treating physician. The study nurse / physician will fill out the appropriate case report form at this stage. Infants who are not eligible for enrolment will be managed as per the treatment protocols of the hospital. All young infants with any moderate-mortality-risk sign or two or more signs of CSI (**Box 1**) will be admitted for injectable antibiotics by the treating physician. The CRP blood test will be conducted 48 hours post-admission. The study screening, enrolment and randomization team will re-screen the admitted infant using an appropriate case report form to assess the infant’s status and eligibility for the trial. Infants will be enrolled in the trial if they are clinically well at the time of the visit (none of the PSBI signs) and have a CRP <10 mg / l. However, if the treating physician has any concerns or reasons for wanting the child to remain in the hospital, then the child will not be considered for randomisation and will be excluded from the study.

See the study approach for screening, enrolment and randomisation in **Figure 1** and the implementation strategy in **Table 2**. In addition, study information regarding objectives and procedures will be posted in the labour and delivery wards, antenatal care clinics and postnatal clinics in the participating hospitals.

**Figure 1 F1:**
[figure not shown]
Study approach for screening, enrolment and management of sick infants. *Signs of possible serious bacterial infection (PSBI): convulsions, not able to feed at all, stopped feeding well, severe chest indrawing, body temperature ≥38°C, body temperature <35.5°C, movement only when stimulated, no movement at all, fast breathing in <7 days. †[31]. ‡Clinically well on day 3 defined as absence of all signs of critical illness or CSI, laboratory test negative, and family lives in a catchment area where a follow-up can be accomplished. CSI – clinical severe infection, IV – intravenous, IM – intramuscular, PSBI – possible serious bacterial infection

**Table 2 T2:** Implementation Strategy for Intervention and Control Arms

Activity	What	Who	When	Where	How
Case identification	Detection of cases	Screening, enrolment and randomisation team with hospital staff	The sick young infant is brought by the family for consultation	OPD or general or paediatric emergency department of the hospital	Clinical assessment
Screening, randomisation and enrolment	Detection of eligible cases	Screening, enrolment and randomisation team	The young infant is seen by the hospital staff and the study staff	OPD or general or paediatric emergency department of the hospital	Clinical assessment, administering informed consent, randomisation and enrolment
Hospitalisation	Admission and treatment with recommended WHO injectable antibiotics	Hospital staff	After pre-enrolment	Inpatient department	After clinical assessment and pre-enrolment
Laboratory test	C-Reactive Protein (CRP) testing	Hospital staff	48-72 hours after admission	Inpatient department	Bedside test using WHO provided kits
Eligibility for the trial	Assess infants’ status using an appropriate case report form	Screening, enrolment and randomisation team	48-72 hours after admission	Inpatient department	Checking the presence of clinical signs and CRP test results and obtaining informed consent before enrolment
Enrolment and randomisation	Enroll and randomise to the treatment arm	Screening, enrolment and randomisation team	48-72 hours after admission	Inpatient department	Using QR codes
Treatment provision (intervention arm)	Discharge from the hospital on oral amoxicillin	Mothers / caretakers will give oral antibiotic	After discharge from the hospital	At home on an outpatient basis	Practical demonstration of giving the first dose in front of the mother / caregiver
Treatment provision (control arm)	Continue hospitalisation for injectable antibiotics and supportive care	Hospital / study staff	After enrolment, consent and randomisation	Hospital	Giving injectable therapy
Treatment documentation	Follow-up for treatment documentation	Treatment documentation team	Days 4, 8 of initial admission	Intervention arm: patients' homes or OPD	Intervention arm: asking mothers and checking medicine bottles
				Control arm: hospital where the patient is admitted	Control arm: hospital inpatient treatment records
Supervision	Sub-sample on follow-up days for quality assurance	Study supervisor	Days 4, 8 and 15 of initial admission	Intervention arm: patients’ homes and OPD	Verification and substantiating assessment
				Control arm: hospital where the patient is admitted and patients’ homes	
Outcome assessment	Outcome assessment	Independent Outcome Assessment Team	Day 2, 4, 8, 15 post-randomisation and if the patient deteriorated in between	Intervention arm: patients’ homes or a hospital if the patient was admitted	Clinical assessment and filling outcome assessment form
				Control arm: hospital where the patient is admitted and at home after discharge	

OPD – outpatient department, CRP – C-reactive protein, CRF – case report form, WHO – World Health Organization

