### Treatment documentation

The study treatment documentation and compliance team will document the treatment received in the hospital (control) and home (intervention) from days one to seven after enrolment. For infants in the control arm, the documentation of treatment received will be captured from the hospital inpatient treatment charts. For infants in the intervention arm, the documentation of treatment received will be captured through mother reports or physicians' outpatient department (OPD) records.

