### Outcome assessment

Due to the nature of the treatment, the trial cannot be blinded. To reduce potential measurement bias, we will use Independent Outcome Assessors (IOA) who will not be associated with the treatment of the infant. The IOAs who will be the Outcome Assessment Team members will conduct outcome assessment visits using the designated days four, eight and 15 post-admission. In the hospital arm, the outcome visits on day four will be done in the hospital, while on days eight and 15, visits will be done at home (or in the hospital or where ever the infant may have moved to). In the outpatient arm, the outcome visits on days four, eight, and 15 will be done at home or where ever the infant may have moved to. If the infant is not able to be seen on the specified day, then a window of additional time will be allowed for outcome follow up, i.e. for day four visit, an additional 24 hours; for day eight and day 15 visits, an additional 48 hours. The outcome team will continue to visit the family during this time window to complete these visits.

Outcomes will only be ascertained by the IOAs per the criteria mentioned above under outcomes. A case will be considered to have a poor clinical outcome if it is confirmed by the IOA.

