### Patient safety

The study procedures and data collection will not pose any significant physical, psychological, social, legal or other kinds of risks to the participants. Clinical assessment and illness management, including the provision of drugs to be used in this study, are routinely used in clinical practice. Every enrolled subject will be followed up till the completion of treatment and assessed on day 15 of the enrolment. Poor clinical outcomes (except deaths) will receive an appropriate change of antibiotic therapy according to standard clinical practice. Those needing hospitalisation will be referred and admitted to the sub-district / district / tertiary care hospitals immediately for appropriate management as required. Other discomforts to caregivers might include a longer waiting time for data collection. However, the procedures will be explained in detail, and any queries by parents will be answered. The mobile phone number of the responsible study staff and study supervisors will be provided to all participants’ caregivers so that they could reach them if needed.

We will counsel and empower the mother / caregivers / families at enrolment, and all follow-up visits to 1) recognise danger signs or signs of illness and seek care and 2) know when to return to the hospital for follow-up care. We will train the mother / caregiver / family on the quantity, frequency and process of giving oral antibiotics at home. Systems will be in place in the hospital to provide emergency and rescue care in case of any adverse event or facilitate referral to a higher facility if required.

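### The Outcome assessment row of Table 2 counts visits from randomisation while the primary outcome counts from start of therapy, so the day-8 and day-15 visits could fall 2-3 days late

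*Protocol article*

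**What the plan says.** The Outcomes section times every component of the primary outcome from initiation of therapy. The death component is "death between randomisation (day three of initiation of therapy) and day 15 of initiation of therapy". Critical illness or another serious infection is looked for on days four and eight. The last component is "presence of any sign of CSI on day eight of initiation of therapy".

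The Outcome assessment section has the assessors visit on the "designated days four, eight and 15 post-admission", with 24 extra hours allowed for day 4 and 48 for days 8 and 15. The abstract counts the same three days from the start of treatment. Follow-up ends observation on day 15 from admission. In Table 2, the Supervision row (days 4, 8, 15) and the Treatment documentation row (days 4, 8) also count from admission.

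Two places differ. The Outcome assessment row of Table 2 gives "Day 2, 4, 8, 15 post-randomisation and if the patient deteriorated in between", and Patient Safety says "assessed on day 15 of the enrolment".

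Table 2 also dates randomisation twice. The Screening, randomisation and enrolment row, set in the outpatient or emergency department, lists "Clinical assessment, administering informed consent, randomisation and enrolment". The later Enrolment and randomisation row reads "Enroll and randomise to the treatment arm Screening, enrolment and randomisation team 48-72 hours after admission".

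**The concern.** The non-fatal components of the primary outcome depend on the day on which signs are looked for. The row that tells assessors when to visit uses a different time origin from the one that defines the outcome, and randomisation lies two to three days after admission. A site that schedules from that row would look for CSI signs some days after the defined day. Signs present on day 8 may have resolved by then, and new illness may have appeared. If seven sites resolve the conflict differently, the pooled endpoint mixes assessment days. Supervisors, whose row counts from admission, would also be checking on different days from those on which the assessors measure.

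**Working it through.** **Inputs**

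- Endpoint days 4, 8 and 15, and randomisation on day three of therapy: Outcomes section.
- Randomisation at 48-72 h after admission: Enrolment and randomisation row of Table 2.
- Visits on days 2, 4, 8, 15 after randomisation: Outcome assessment row of Table 2.
- Windows: Outcome assessment section. With +24 h, day 4 may be done on days 4-5. With +48 h, day 8 may be done on days 8-10 and day 15 on days 15-17.
- Assumption: admission and start of therapy fall on the same day, numbered day 1.

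**Step 1: reproduce the protocol's own figure.** Randomisation day R = 1 + h/24. At 48 h, R = 1 + 2 = 3, which agrees with the Outcomes section. At 72 h, R = 1 + 3 = 4.

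**Step 2: move the Table 2 visits to the therapy clock.** Therapy day = R + v - c, where v is the visit label. If the day of randomisation is numbered day 1, c = 1; if it is numbered day 0, c = 0. The protocol does not say which, so both are shown. For example, at 48 h with c = 1, the visit labelled day 8 falls on 3 + 8 - 1 = day 10.

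| Randomised at | c | Label 2 | Label 4 | Label 8 | Label 15 | Shift (days) |
|---|---|---|---|---|---|---|
| 48 h | 1 | 4 | 6 | 10 | 17 | 2 |
| 48 h | 0 | 5 | 7 | 11 | 18 | 3 |
| 72 h | 1 | 5 | 7 | 11 | 18 | 3 |
| 72 h | 0 | 6 | 8 | 12 | 19 | 4 |

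With the same numbering on both clocks (c = 1), the shift equals the elapsed 48-72 h, that is 2-3 days. The 4-day figure needs both the latest randomisation and day-0 numbering.

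**Step 3: compare with the windows.**

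- Label 8 falls on day 10, the last permitted day, with a 2-day shift, and on day 11 or 12, outside the window, otherwise.
- Label 15 falls on day 17, the last permitted day, with a 2-day shift, and on day 18 or 19, outside, otherwise.
- Label 4 falls on days 6-8, outside the day-4 window in every case. In the last line of the table it happens to land on therapy day 8, but it would be filed as the day-4 visit.
- Label 2 falls on day 4 or 5, inside the day-4 window, in three of the four cases.

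**Step 4: after correction.** With the outcome row counted from initiation of therapy, the visits fall on days 4, 8 and 15 with no shift. A day-2 entry would then precede randomisation on day 3, so it cannot simply be carried over.

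**Step 5: the presentation row.** If randomisation did take place at presentation, R = 1, and with c = 1 the visits fall on days 2, 4, 8 and 15, with no delay. It cannot take place then, because a negative C-reactive protein test at 48 h is an eligibility requirement.

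**The case against.** The strongest reply is that the endpoint clock is stated clearly in the Outcomes section, that most of the document agrees with it, and that only one row of Table 2 departs from it. Staff work from a Manual of Operations that is not shown. This stands as far as it goes: the delay is conditional on a site following that row. It does not remove the conflict, because that row is the one that sets out the assessors' work.

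Stronger conclusions are tempting, and the document does not support them:

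- **That the day-4 component cannot register an event in infants randomised near 72 h.** A visit on the day of randomisation would be uninformative, but the +24 h window allows a later one. The same signs count again on day 8, and Table 2 adds an assessment if the infant deteriorates in between. The day-2 visit also usually falls in the day-4 window.
- **That deaths are counted over a longer period.** The Outcomes section closes the death window on day 15 of therapy. A later contact changes when a death is learned of, not whether its date qualifies.
- **That a day-8 visit after treatment has ended is itself an error.** Treatment lasts seven days in total, so the defined day-8 assessment already follows it.
- **That the presentation row causes late visits.** Step 5 shows that it does not.
- **That the span "from days one to seven after enrolment" in Treatment documentation shifts the endpoint.** It concerns treatment records, not outcome visits.

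**Conclusion.** The contradiction is real and touches the primary endpoint, but it is narrow. One row of Table 2 and one sentence in Patient Safety use randomisation or enrolment as the time origin; everything else that dates the outcome visits uses initiation of therapy or admission. Followed literally, the row makes the day-8 and day-15 visits about 2-3 elapsed days late, on about therapy days 10-11 and 17-18, at the edge of the +48 h window or beyond it. The main consequence is that the day-eight CSI component is read on the wrong day. The day-4 component is usually rescued by the extra day-2 visit.

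This assumes that admission and start of therapy coincide, that randomisation is at 48-72 h, and that a site follows the row. The shift applies to both arms, so it bears on endpoint definition and event rates rather than directly favouring one arm. The effect on the event rate cannot be computed, because the document gives no figures on signs resolving or appearing between day 8 and days 10-11. The presentation row is a separate drafting inconsistency with no effect on timing.

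**What to change.** - Put the Outcome assessment row of Table 2 and the Patient Safety sentence on the time origin of the Outcomes section: days 4, 8 and 15 of initiation of therapy.
- Remove the day-2 entry, or explain what it is for and on which clock it runs.
- Reconcile the presentation row of Table 2 with the row that randomises at 48-72 h.
- Check that visit-due dates programmed in the data system use the clock of the Outcomes section.
- Count deaths by date of death, to day 15 of therapy.

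The cost is edits to two rows of Table 2 and one sentence, plus a check of the programmed due dates. No new visits and no change to the endpoint are needed.

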### Randomisation to treatment arms

WHO staff in Geneva not associated with site work prepared the randomisation list in blocks of four, six and eight and shared it with the Regional Triangle Institute (RTI), the study Data Coordination Centre (DCC). Allocation concealment was ensured using QR randomisation codes. Randomization was in a 1:1 ratio. RTI produced a list of encrypted QR codes and has these printed on labels based on the randomisation scheme for each study site. RTI transmitted the printed QR code blue colour labels to the sites.

Each hospital within a study site will have a single set of QR codes that all screening and enrolment team members must use, even if the screening and enrolment are taking place in different locations within the hospital. After determining eligibility, the data collector will take the QR code label next in the sequence from the list at their facility and scan this to obtain the randomisation number.

### Sample size

We will enrol a total of 5250 participants in the trial across study sites. Power calculations assumed 1:1 randomised, a one-sided type I error rate α of 0.025 (equivalent to a two-sided 95% confidence interval), and a loss to follow-up or withdrawal rate of 10%. The non-inferiority margin for the poor clinical outcome was selected as a relative risk of 1.40 for the outpatient group as compared to the standard inpatient group. This margin was selected based on the previous trials [6,7]. **Table 3** presents statistical power for trial outcomes varying the potential cumulative incidence of poor clinical outcomes in the standard inpatient group. We will have >88% power to test for non-inferiority if the cumulative incidence of poor clinical outcomes is 5-10% in the inpatient group.

**Table 3 T3:** Statistical power calculations for incidence of poor clinical outcome

		Cumulative incidence of poor clinical outcome in standard inpatient arm		
		**10.0%**	**7.5%**	**5.0%**
Statistical power for poor clinical outcome	Noninferiority margin: Relative risk of 1.40	96.6%	97.5%	88.4%

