**Methods:**

A multi-centre, individually randomised, open-label trial will be conducted in seven sites in six countries: Bangladesh, Ethiopia, India (two sites), Nigeria, Pakistan and Tanzania. A common protocol will be used with the same study design, including the participants, intervention, comparison, outcomes, quality control, and analysis procedures. 0-59 days old infants presenting with moderate-mortality risk signs (low body temperature (<35.5°C), movement only when stimulated, stopped feeding well) or two or more signs of clinical severe infection (CSI) will be assessed and pre-enrolled. After 48 hours of hospital stay, clinically stable infants with a negative C-reactive protein test will be randomised either to hospital discharge on oral amoxicillin (intervention) or continued hospitalisation (control) arm. The intervention arm will receive oral amoxicillin for five days, whereas the control arm will receive injection gentamicin plus injection ampicillin for five more days plus supportive therapy if needed. We plan to enrol 5250 eligible young infants, 2625 infants in each of the two study arms. An experienced, well-trained independent outcome assessor will visit all enrolled cases on days 4, 8 and 15 after the initiation of treatment to assess the study outcomes in both intervention and control arms. The primary outcome of poor clinical outcome defined as death between randomisation and day 15 of initiation of treatment, deterioration during the 7-day treatment period, or persistence of the presenting sign of CSI at the end of the 7-day treatment period will be compared to assess if an early discharge and outpatient treatment leads to superior or at least non-inferior clinical outcome than continued inpatient treatment. The harmonisation of activities, including methods and processes, will be carried out diligently. Central training will be conducted by the WHO coordinating team, a central data coordination centre to collate all data, standardisation exercises for all clinical signs and internal and external monitoring. All the selected sites have extensive research experience. Through regular online and physical meetings, data-based monitoring, and physical site visits by WHO monitors, quality assurance and harmonisation will be ensured. This trial has been approved by the WHO and local site institutional ethics committees.

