Of all young infants with any sign of CSI who received outpatient treatment in the AFRINEST study, 1.3% died up to 15 days after the initiation of treatment. Of those who died, 39.7% died within the first 48 hours of treatment. Among those who survived and were assessed at 48 hours of treatment, three-quarters of infants (73.9%) had no signs of illness. Of these infants who recovered by 48 hours, 0.4% died between day three and day 15. In contrast, mortality between day three and day 15 was higher among infants who still had the presenting sign at 48 hours (0.7%) or those who deteriorated (presence of new CSI sign / critical illness sign) at 48 hours (8.0%) (secondary analysis, unpublished data).

In high-income settings, infants with clinical suspicion of sepsis are hospitalised, and parenteral antibiotics are initiated after taking samples for sepsis screening and blood culture. After 48 hours, if the laboratory tests are negative and the infant is clinically well, antibiotics are stopped, and the infants are discharged [27-29]. However, this is hardly ever done in the LMICs, where once started, the parenteral antibiotics are continued for 7-10 days. We need evidence of whether sick young infants with moderate-mortality risk can be discharged early from the hospital.

The primary objective of this trial is to measure the effect of early discharge on an oral amoxicillin treatment on poor clinical outcomes compared with inpatient treatment in young infants 0-59 days old with moderate-mortality risk or two or more signs of CSI. We hypothesise that the majority of infants who improve by 48 hours will need shorter hospitalisation.

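### Table 3 is not the power of a test against a relative risk of 1.40: at 5% incidence that power is about 75%, not 88.4%, and the table falls where power must rise

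*Protocol article*

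**What the plan says.** The Sample size section states: "We will enrol a total of 5250 participants in the trial across study sites". The Methods paragraph of the abstract splits this into 2625 per arm. The calculation uses 1:1 allocation, one-sided alpha 0.025 and 10% loss to follow-up or withdrawal. The margin is given as a ratio: "The non-inferiority margin for the poor clinical outcome was selected as a relative risk of 1.40 for the outpatient group". Table 3 repeats it in its row label, "Noninferiority margin: Relative risk of 1.40", and prints:

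| Control incidence | 10.0% | 7.5% | 5.0% |
|---|---|---|---|
| Stated power | 96.6% | 97.5% | 88.4% |

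The text concludes: "We will have >88% power to test for non-inferiority if the cumulative incidence of poor clinical outcomes is 5-10% in the inpatient group". No absolute margin and no assumed true relative risk appear in the article. The Data analysis section plans a chi-square comparison of proportions and a risk difference with a 95% confidence interval.

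**The concern.** Two things do not fit.

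- Sample size, alpha, loss and margin are the same in all three columns, and only the control incidence changes. A higher incidence gives more events, so power against a fixed relative margin should rise from right to left across the table. It falls instead, from 97.5% at 7.5% to 96.6% at 10%.
- The 5% entry, on which the claim of more than 88% rests, looks too high for a ratio margin of 1.40 with this many infants.

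This is the article's only statement of power. If it is too favourable, an inconclusive result at low incidence would be read as evidence against early discharge when the trial simply had less power than stated. A low incidence is possible. Infants are randomised only if they have no signs and a negative CRP, and the introduction reports for an earlier study: "Of these infants who recovered by 48 hours, 0.4% died between day three and day 15". That figure counts deaths only, among outpatient-treated infants, so it hints at a low composite rate but does not establish one.

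**Working it through.** **Inputs.** From the article: 2625 per arm less 10%, so n = 2625 × 0.9 = 2362.5; one-sided alpha 0.025, so z = 1.96; margin RR 1.40; control risk p of 0.10, 0.075 and 0.05. Assumed, because the article does not say: the true risks are equal (true RR 1.0).

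**Step 1: reproduce the printed figures.** Treat the margin as a fixed absolute difference of 0.40 × p, with p taken as known, and test the risk difference:

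power = Φ(0.40p / √(2p(1−p)/n) − 1.96)

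- p = 0.05: margin 0.020, SE 0.00634, ratio 3.154; Φ(1.194) = 88.4%, as printed.
- p = 0.075: margin 0.030, SE 0.00766, ratio 3.915; Φ(1.955) = 97.5%, as printed.
- p = 0.10: margin 0.040, SE 0.00873, ratio 4.583; Φ(2.623) = 99.6%, printed as 96.6%.

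Two cells match to the decimal and the third does not.

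**Step 2: test the stated margin.** On the log relative risk scale:

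power = Φ(ln 1.40 / √(2(1−p)/(pn)) − 1.96), with ln 1.40 = 0.3365

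- p = 0.10: SE 0.0873, ratio 3.855; Φ(1.895) = 97.1%.
- p = 0.075: SE 0.1022, ratio 3.293; Φ(1.333) = 90.9%.
- p = 0.05: SE 0.1268, ratio 2.653; Φ(0.693) = 75.6%.

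Both formulas contain the same term √(pn/(2(1−p))). Step 1 multiplies it by 0.40 and Step 2 by 0.3365, which is the whole gap between the two sets of figures. The term increases with p, so power must rise with incidence under either formula.

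**Step 3: check other ratio tests.**

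| Test against RR 1.40 | 10% | 7.5% | 5% |
|---|---|---|---|
| Log relative risk | 97.1% | 90.9% | 75.6% |
| Farrington-Manning ratio score | 96.9% | 90.5% | 75.4% |
| Linear contrast, p1 − 1.4·p0 | 96.5% | 89.6% | 73.6% |
| Simulated log relative risk, 400,000 trials per cell | 96.9% | 90.6% | 75.4% |
| Printed in Table 3 | 96.6% | 97.5% | 88.4% |

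**Step 4: look for inputs that rescue the table.** With no loss at all (2625 per arm), log relative risk power at 5% is 79.9%. Other variants tried were one-sided alpha 0.05, loss applied as N/1.1, and ordinary two-proportion power for p against 1.4p. None, with equal true risks, gives all three printed cells.

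**Step 5: where 88% is reached.** Log relative risk power is 83.2% at 6% incidence, 86.2% at 6.5%, 88.3% at 6.9% and 88.7% at 7%. Below the table's range it is 66% at 4%, 53% at 3% and 38% at 2%.

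**The case against.** The strongest reply is that the Data analysis section plans a risk difference, and that 88.4% and 97.5% are correct arithmetic for a risk difference. On that view the fault is a missing absolute margin, and the power claim stands. The arithmetic is indeed right for that test. But the article defines non-inferiority only as a relative risk of 1.40, and a fixed margin of 2 percentage points is a different hypothesis. Suppose control incidence turned out to be 3%. A 2-point margin then allows a relative risk up to 0.05/0.03 = 1.67. An intervention exactly at RR 1.40 (4.2% against 3%) would pass with probability Φ((0.020 − 0.012)/0.00542 − 1.96) = 31%, not 2.5%. If absolute margins were meant, the article has to state them, so a correction is needed on either reading.

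A second reply is that a small true benefit may have been assumed. On the log scale a true RR of 0.95 gives 85.5% at 5% incidence, and 0.93 gives 88.6% at 5% and 97.5% at 7.5%. The article states no such assumption, and 0.93 gives 99.6%, not 96.6%, at 10%. The point that stands is that 75% is conditional on equal true risks.

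A third is that 96.6% may be a misprint of 99.6%. That is possible. It is equally close to the ratio-scale value of 96.5% to 97.1%, and the article cannot settle which. Either value exceeds 88%, so this cell does not affect the claim at 5%, but it still needs correcting.

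**Conclusion.** The concern holds. Against the stated margin of RR 1.40, power at 5% control incidence is about 75% (73.6% to 75.6% by test) rather than 88.4%. The type II error is about 24%, against 11.6% as printed. At 7.5% incidence power is about 91% (89.6% to 90.9%), against 97.5%. The claim of more than 88% fails from 5% up to roughly 7% incidence, about the lower two-fifths of its own range. The drop from 97.5% to 96.6% is impossible for a single method at a fixed relative margin and true RR. These figures assume 2362.5 evaluable infants per arm, one-sided alpha 0.025 and a true relative risk of 1.0, the last being an assumption on the article's behalf.

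**What to change.** Recompute Table 3 for the relative risk test: about 97% at 10%, 91% at 7.5% and 75% at 5%. Name the test and the assumed true relative risk. Restate the sentence as about 75% power at 5% incidence, with more than 88% only if incidence is about 7% or higher. If the sponsor meant absolute margins, state them (2.0, 3.0 and 4.0 points at the three incidences), say which one the trial will be judged against, and correct the 10% entry to 99.6%. The label and text could then no longer describe the margin as RR 1.40. Columns for 2% to 4% would show how fast power falls, but they are optional.

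The cost is one table and one sentence, and a less favourable stated power. Enrolment stays at 5250. For scale only, 88.4% power at 5% incidence on the log relative risk scale would need about 3342 evaluable per arm, which is 3342/0.9 ≈ 3713 enrolled per arm or about 7426 in total.
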